### Procedure

Subjects fulfilling the general eligibility criteria as determined through the pre-screening will be invited for baseline assessments. During the first visit at the CIMH, subjects will provide written consent for participation. Specific eligibility criteria will be examined by a trained psychologist and a trained psychiatrist specialized in geriatric psychiatry. Individuals fulfilling the diagnostic criteria will then undergo behavioral, neuropsychological, and neurophysiological assessments conducted by the psychologist, and a physical and neuropsychological examination as well as the assessment of the medical history and medication conducted by the psychiatrist. Blood samples will be collected and conserved for analysis of BDNF serum levels and genotypes. After baseline assessments, subjects will be introduced to the respective training procedure by a psychologist. Support during the home-based treatment is also provided. After 60 and 90 days, the assessment of sensorimotor, neurocognitive and neurophysiological functioning will be repeated at the CIMH. Neuropsychological and physical examination including collection of blood samples will be repeated after 60 days. Prior to and after the training, participants will be asked for treatment expectation and evaluation, respectively, using five questions adapted from [42] to uncover motivational and affective aspects of the training. Subjects will not be paid for participation, but will be compensated for their travel costs.

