### Sample size

Previous studies in healthy older humans using sensory training have achieved promising results with medium effect sizes and sample sizes of 41 to 53 subjects [5, 32]. Given that our training includes a multimodal stimulation approach and focuses on motivational enhancement within a virtual training environment, we assume that in our participants the effect of the experimental training program would exceed a medium effect size. To estimate sample size, we use a repeated measures design with one between-factor with two groups and one within-factor with three assessment points [43]. Assuming a medium effect size of Cohen’s f = 0.25, 95% statistical power, a correlation of 0.50 between the dependent measurements, and a two-sided alpha error level of .05, we therefore would need 22 participants in each group. To account for a drop-out rate of about 25% during the training, we will include 30 subjects per group (60 in total).

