### Outcome measures and biological moderators

The assessments will be performed according to the structure depicted in Table 1.

**Table 1 Tab1:** Overview of outcomes, outcome measures, instruments and assessment time points

Outcomes	Outcome measures	Instruments	Assessment time points
**Personal information**	• Age, sex, education, clinical history, medication	• Self reports	• T0, T1, T2
**Frailty assessments**	• Frailty status (pre-frail, frail) • Frailty Index	• Frailty Phenotype • Frailty Index	• T0, T1, T2 • T0, T1, T2
**Brain plasticity in the sensorimotor and somatosensory system**	• Structural and functional parameters of cortical sensorimotor and somatosensory maps • MEP peak-to-peak amplitude and latency	• fMRI motor sequence task, fMRI somato-sensory mapping task • TMS at left primary motor cortex	• T0, T1 • T0, T1
**Biological markers of neuroplasticity**	• BDNF serum blood levels (ng/ml)	• Collection of blood samples	• T0, T1
**Sensorimotor performance**	• SPPB (total score) • CTSIB (total score) • PPT (means)	• SPPB • CTSIB • PPT	• T0, T1, T2 • T0, T1 • T0, T1, T2
**Sensory functioning**	• Visual acuity • Visual contrast sensitivity • Tactile grating thresholds • Fine-touch thresholds • Hearing thresholds	• FrACT • FrACT • JVP domes • Von-Frey filaments • Audiometer	• T0, T1, T2 • T0, T1, T2 • T0, T1, T2 • T0, T1 • T0, T1
**Cognitive testing**	• MMSE (total score) • Mental and motor response speed • Top-down attentional control • Visuospatial working memory capacity • Executive functioning	• MMSE • RTI • AST • SSP • IED	• T0, T1, T2 • T0, T1 • T0, T1, T2 • T0, T1 • T0, T1
**Functional level and quality of life**	• Functional level in frailty • Depression • Overall health status and quality of life • Functional capacity in everyday activities • Falls self-efficacy • Nutritional status	• FEFA • CES-D • SF-36, EQ-5D-5L • MKS • FES-I • MNA	• T0, T1, T2 • T0, T1 • T0, T1, T2 • T0, T1 • T0, T1, T2 • T0, T1

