#### Frailty status

Comparison with other training studies will be possible by using the frailty phenotype [39] as a measure of frailty status as primary outcome. Additionally, we will assess the frailty index [52, 53], which is calculated as the ratio of the number of deficits present out of a total number of 40 deficits assessed, including previous diseases, disability, psychosocial risk factors as well as physical and cognitive impairments [53]. Thus, the frailty index consists of a continuous score between 0 and 1 with higher values representing more pronounced frailty and increased susceptibility to adverse health outcomes [53]. While some studies demonstrated that frailty scores obtained from the two measures are comparable [54, 55], others have suggested that the frailty index might discriminate better at the lower to middle end of the frailty continuum [56] and might be more sensitive to measure change after an intervention [57]. Therefore, we will use both measures in a complementary rather than comparative manner [58].

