#### Neuronal efficiency in the sensorimotor brain system

Age-related decline in sensorimotor performance has been linked to decreased neuronal efficiency in the sensorimotor system with respect to reduced motor cortex excitability [62, 63]. To investigate motor cortex excitability at baseline and after the intervention, we will perform single-pulse transcranial magnetic stimulation (TMS) at the left primary motor cortex (M1) and simultaneous recording of motor-evoked potentials (MEP) at the right abductor pollicis brevis. As measures of motor cortex excitability, we will calculate MEP peak-to-peak amplitudes and latencies. Prior to the stimulation, we will determine individual resting motor threshold (RMT), defined as the stimulation intensity at which at least 6 out of 10 MEPs reached a peak-to-peak amplitude of ≥50 μV [64]. We will then conduct three stimulation runs at 100, 110 and 120% of the RMT intensity in pseudorandomized order. Each run will consist of 20 consecutive stimulations with an inter-stimulus interval of approximately 10 s.

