### Data analysis and handling

We will use mixed repeated measures analyses of variance for each of the outcome variables in order to assess the effect of the training at baseline, after 60 days, and after 90 days, as well as to unveil differences between the two groups. Significant time-by-group interactions will be further examined using post-hoc tests. To evaluate changes through the interventions, pre-post effect sizes will be computed and compared across interventions. The problem of missing data will be handled using multiple imputation.

Data collected in this project will be recorded, stored and analyzed anonymously. A list assigning codes to names will be stored separately under high security standards. Analysis of the data will be of scientific purpose only.

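### The analysis section plans three visits for every outcome, but Table 1 measures 12 of 24 outcomes only at baseline and day 60, and the protocol contradicts itself on what is repeated at day 90

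*Protocol article*

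**What the plan says.** Four places in the protocol article bear on what is measured at day 90.

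- **Data analysis and handling.** Mixed repeated-measures ANOVA is planned "for each of the outcome variables in order to assess the effect of the training at baseline, after 60 days, and after 90 days". Missing data are to be handled by multiple imputation.
- **Procedure.** "After 60 and 90 days, the assessment of sensorimotor, neurocognitive and neurophysiological functioning will be repeated at the CIMH". The next sentence reads "Neuropsychological and physical examination including collection of blood samples will be repeated after 60 days".
- **Neuronal efficiency in the sensorimotor brain system.** TMS is done "To investigate motor cortex excitability at baseline and after the intervention".
- **Table 1.** T0 is baseline, T1 is day 60 and T2 is day 90. Half of the outcome rows list T0 and T1 only, among them fMRI, TMS and the row "Functional capacity in everyday activities" (MKS).

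The Sample size section assumes "one between-factor with two groups and one within-factor with three assessment points". The Interventions section divides the 90-day sensorimotor training into three consecutive 30-day phases: unimodal discrimination, bimodal integration, and finally the sensorimotor tasks (cycling, grasping, hand coordination). The Objectives predict refined sensorimotor maps and a pre-to-post rise in serum BDNF.

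**The concern.** An analysis with a three-level time factor needs three scheduled measurements. Where Table 1 schedules two, the stated model does not exist for that outcome, and an analyst would have to choose a substitute after the fact.

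Timing matters as well. The rows without a day-90 visit include every brain measure, the only blood marker and the only dedicated balance test, which carry the trial's mechanistic hypothesis. If they stop at day 60, they are read before the sensorimotor phase has begun. A result reported as pre-to-post would then be taken for the effect of the full 90-day programme when only its first two phases had been delivered.

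**Working it through.** **Step 1. Count the outcome rows in Table 1** (personal information excluded).

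| Schedule | Outcome rows | Count |
|---|---|---|
| T0, T1, T2 | Frailty Phenotype, Frailty Index, SPPB, PPT, visual acuity, contrast sensitivity, tactile gratings, MMSE, AST, FEFA, SF-36/EQ-5D-5L, FES-I | 12 |
| T0, T1 only | fMRI, TMS, BDNF, CTSIB, fine touch, hearing, RTI, SSP, IED, CES-D, MKS, MNA | 12 |

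So 12 of 24 rows have no T2 (12 of 25 if SF-36 and EQ-5D-5L are counted separately).

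**Step 2. Set the text beside the table.**

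| Text | What the text implies | Table 1 |
|---|---|---|
| Data analysis | every outcome at three visits | 12 rows at two visits |
| Procedure, neurophysiological | repeated at days 60 and 90 | fMRI, TMS: last at day 60 |
| Procedure, neurocognitive | repeated at days 60 and 90 | RTI, SSP, IED: last at day 60 |
| Procedure, sensorimotor | repeated at days 60 and 90 | CTSIB: last at day 60 |
| TMS section | after the intervention | TMS: day 60 of 90 |
| Procedure, blood | day 60 | BDNF: day 60 (agrees) |

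**Step 3. Can imputation close the gap?** No. For these rows T2 is unscheduled for every participant. There is no observed T2 value from which to estimate its mean, its variance or its correlation with earlier visits.

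**Step 4. Place day 60 in the training.** Two phases of 30 days take 60 days. A day-60 measurement therefore falls at the end of phase two, before phase three.

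**Step 5. Reproduce the sample size.** The inputs, from the Sample size section, are f = 0.25, correlation ρ = 0.50, α = 0.05, k = 2 groups and m = 3 visits. For the group-by-time interaction:

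λ = f² × N × m / (1 − ρ), with df = (k − 1)(m − 1) and (N − k)(m − 1).

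- N = 44: λ = 0.0625 × 44 × 3 / 0.5 = 16.5, F(2, 84), power 95.6%.
- N = 42: power 94.6%.

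So 22 per group is correct for the stated design, and 22 / 0.75 = 29.3 rounds up to 30 per group.

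**Step 6. Same test with two visits.** This assumes that f and ρ carry over unchanged.

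- N = 44, m = 2: λ = 0.0625 × 44 × 2 / 0.5 = 11.0, F(1, 42), power 90.0%.
- 95% power would need N = 54 (27 per group): λ = 13.5, F(1, 52), power 95.0%.

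**Step 7. Baseline-adjusted alternative for two visits.** In units of the outcome variance, a change score has variance 2(1 − ρ) = 1.00, and the baseline-adjusted day-60 value has 1 − ρ² = 0.75. Then λ = 11.0 / 0.75 = 14.7 with F(1, 41), and power is about 96%. On the plan's own assumptions, the adjusted comparison recovers what the loss of a visit costs.

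**The case against.** **The ANOVA wording is loose, but the model can still be used.** A mixed repeated-measures model accepts a two-level time factor, and half of the rows, the primary outcome among them, have three visits. This stands, and it limits the point. The article nevertheless names three visits for each outcome, and does not say that some will be analysed at two or that their endpoint is mid-training.

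**The day-60 sentence on examinations is not itself an error.** It can be read as the psychiatrist's examination plus blood sampling, which agrees with the BDNF row. That is a fair reading. For the same reason, MMSE at T2 is a contradiction only if MMSE belongs to that examination, which is not stated. The conflict lies in the sentence before it and in the analysis section.

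**Power.** A reader might infer that the protocol promises 95% for every outcome and breaks that promise. It does not: the Sample size section gives one general calculation, and 90% would be no deficiency for secondary outcomes.

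**Frailty Index.** A reader might go further and infer that the day-90 index cannot be computed, because its deficits are described as "including previous diseases, disability, psychosocial risk factors as well as physical and cognitive impairments" while CES-D, MKS and MNA stop at day 60. The documents do not support this. The 40 items are not listed, and Table 1 schedules the index itself at T2. Each named domain also has a possible T2 source: self-reported clinical history and medication for previous diseases, FEFA for disability, SF-36 for psychosocial factors, SPPB and the phenotype measures for physical impairment, and MMSE and AST for cognition. Any figure for a shift in the index would rest on guesses about which items it contains.

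**Choice of method.** A baseline-adjusted comparison instead of a two-visit interaction test is a choice between valid methods. That is true; step 7 is the reason for preferring it.

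**Conclusion.** The point holds as a conflict between schedule and analysis. The three-visit ANOVA cannot be run for 12 of the 24 outcome rows, and multiple imputation does not repair this. The text and Table 1 disagree on day 90 for at least six of those rows (fMRI, TMS, CTSIB, RTI, SSP, IED). If Table 1 is right, all 12 give a result at day 60 of 90, before the third training phase, and describing any of them as pre-to-post would misstate what was tested.

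The frailty phenotype is scheduled at all three visits, so the primary outcome and the visit structure behind its sample size are untouched. The power consequence is minor: 95.6% for three visits against 90.0% for the same interaction test on two, at 44 completers, provided f = 0.25 and ρ = 0.50 apply to both. For the Frailty Index there is only something to confirm. The matter should be corrected, but it does not threaten the main comparison.

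**What to change.** 1. Reconcile the Procedure, TMS and Data analysis sections with Table 1, so that one schedule states what is measured at day 90.
2. For every outcome that remains at T0 and T1 only, replace the three-visit ANOVA by a comparison of the groups at day 60 adjusted for the baseline value. Report it as a mid-training effect, and reword the pre-to-post BDNF and brain hypotheses to match.
3. State that multiple imputation covers missed visits, not visits that were never scheduled.
4. Add to the Sample size section that the power figure describes three-visit outcomes, and that the same interaction test on two visits has about 90% under the same assumed f and correlation.
5. Confirm that the same Frailty Index deficits are measured at T0, T1 and T2.

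The cost is wording in the protocol and analysis plan, with no extra participants. If the reconciliation shows that day-90 measurements were intended for some of these outcomes, Table 1 changes, and those visits carry the cost of the added assessments.

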### Randomization and blinding

Subjects will be randomly allocated on a 1:1 ratio to either the experimental or control condition. The randomization schedule will be generated electronically by a researcher not involved in the assessments. Group allocations will be kept in sequentially numbered sealed opaque envelopes. Participants will be informed about the random allocation procedure. Blinding of the investigator will not be possible because the investigator will conduct parts of the assessments and training procedures.

### Sample size

Previous studies in healthy older humans using sensory training have achieved promising results with medium effect sizes and sample sizes of 41 to 53 subjects [5, 32]. Given that our training includes a multimodal stimulation approach and focuses on motivational enhancement within a virtual training environment, we assume that in our participants the effect of the experimental training program would exceed a medium effect size. To estimate sample size, we use a repeated measures design with one between-factor with two groups and one within-factor with three assessment points [43]. Assuming a medium effect size of Cohen’s f = 0.25, 95% statistical power, a correlation of 0.50 between the dependent measurements, and a two-sided alpha error level of .05, we therefore would need 22 participants in each group. To account for a drop-out rate of about 25% during the training, we will include 30 subjects per group (60 in total).

### Interventions

#### Experimental condition

The interactive tablet-based sensorimotor intervention will consist of three consecutive training phases with each phase comprising 30 days (90 days in total). The first phase will consist of unimodal sensory discrimination tasks in the visual, auditory and tactile domain to increase distinctiveness and acuity of cortical sensory representations. In the second phase, subjects will be trained on bimodal sensory integration using visual-auditory, visual-tactile and auditory-tactile tasks. Bimodal sensory integration will require subjects to process stimuli of two different perceptual modalities and judge whether the two stimuli are synchronous or not. These tasks are assumed to increase temporal acuity for multisensory integration and to promote plasticity in perceptual integration brain networks [44, 45]. Unimodal and bimodal stimuli are presented through the tablet involving explicit answers on the tablet’s touch screen. The third phase will require participants to process bimodal sensory information in order to control a sensorimotor response, in the form of visual-auditory guided cycling, visual-tactile determined grasping, and auditory-visual controlled hands coordination. In these sensorimotor integration tasks, sensory input must be interpreted and integrated in terms of the current state of the motor system to continuously adjust motor commands and behavior [46]. These tasks aim at improving motor acuity, i.e. to increase precision and reduce variability of motor performance by increasing the signal-to-noise ratio in sensorimotor brain networks [47, 48]. For tactile, cycling, and grasping tasks, we will use external devices that are wirelessly connected to and controlled by the tablet (i.e. a Braille display device for tactile tasks, a customized ergometer for cycling tasks, and a handgrip dynamometer for grasping tasks).

Each daily training session will last 30 min allowing self-determined breaks in between. The training tasks will be embedded in a container application featuring a virtual environment of a gaming nature [34]. Performing the daily training tasks, participants can earn tickets to progress on a virtual journey throughout European cities. To enhance training motivation and efficacy, the program will include a customized application environment as well as personally relevant reinforcers (pictures, sounds) individually embedded in the tasks. To enhance training motivation, task difficulty will be dynamically adapted to provide a positive feedback percentage of 70–80%. Accordingly, the adaptive difficulty manipulation should produce sustained sensory and sensorimotor challenges, thereby promoting lasting neural changes and transfer effects [34, 49]. For monitoring and analysis purposes, training data including duration and achievements will be automatically collected by the app and sent to a dedicated server on a daily basis.

#### Control condition

The control intervention will be a self-developed tablet-based relaxation training encompassing daily 30-min sessions across a total training duration of 90 days, which do not include any of the critical features of the sensorimotor training app (i.e. multimodal sensorimotor training, adaptive algorithm, personalized feedback) using stimulating and variable exercises. Training sessions will require participants either to watch relaxation videos consisting of nature scenes or to follow verbally guided relaxation exercises, alternating on a regular basis. Relaxation exercises encompass various relaxation techniques, such as autogenic training, breathing meditation, mindfulness practice, or imaginary journeys. At the end of each session, participants complete a short questionnaire about their affective state including items from the German version of the Positive and Negative Affect Schedule (PANAS) [50, 51]. Training data collected by the app include responses to the post-training questionnaire as well as total amount of time engaged in the daily training.

### Outcome measures and biological moderators

The assessments will be performed according to the structure depicted in Table 1.

**Table 1 Tab1:** Overview of outcomes, outcome measures, instruments and assessment time points

Outcomes	Outcome measures	Instruments	Assessment time points
**Personal information**	• Age, sex, education, clinical history, medication	• Self reports	• T0, T1, T2
**Frailty assessments**	• Frailty status (pre-frail, frail) • Frailty Index	• Frailty Phenotype • Frailty Index	• T0, T1, T2 • T0, T1, T2
**Brain plasticity in the sensorimotor and somatosensory system**	• Structural and functional parameters of cortical sensorimotor and somatosensory maps • MEP peak-to-peak amplitude and latency	• fMRI motor sequence task, fMRI somato-sensory mapping task • TMS at left primary motor cortex	• T0, T1 • T0, T1
**Biological markers of neuroplasticity**	• BDNF serum blood levels (ng/ml)	• Collection of blood samples	• T0, T1
**Sensorimotor performance**	• SPPB (total score) • CTSIB (total score) • PPT (means)	• SPPB • CTSIB • PPT	• T0, T1, T2 • T0, T1 • T0, T1, T2
**Sensory functioning**	• Visual acuity • Visual contrast sensitivity • Tactile grating thresholds • Fine-touch thresholds • Hearing thresholds	• FrACT • FrACT • JVP domes • Von-Frey filaments • Audiometer	• T0, T1, T2 • T0, T1, T2 • T0, T1, T2 • T0, T1 • T0, T1
**Cognitive testing**	• MMSE (total score) • Mental and motor response speed • Top-down attentional control • Visuospatial working memory capacity • Executive functioning	• MMSE • RTI • AST • SSP • IED	• T0, T1, T2 • T0, T1 • T0, T1, T2 • T0, T1 • T0, T1
**Functional level and quality of life**	• Functional level in frailty • Depression • Overall health status and quality of life • Functional capacity in everyday activities • Falls self-efficacy • Nutritional status	• FEFA • CES-D • SF-36, EQ-5D-5L • MKS • FES-I • MNA	• T0, T1, T2 • T0, T1 • T0, T1, T2 • T0, T1 • T0, T1, T2 • T0, T1

*AST* Attention Switching Task, *BDNF* Brain-derived neurotrophic factor, *CES-D* Center for Epidemiologic Studies Depression Scale, *CTSIB* Clinical Test of Sensory Integration of Balance, *EQ-5D-5L* EuroQol-5D-5L, *FEFA* Frail Elderly Functional Assessment, *FES-I* Falls Efficacy Scale – International Version, *fMRI* Functional magnetic resonance imaging, *FrACT* Freiburg Vision Test, *IED* Intra-Extra Dimensional Set Shift, *MEP* Motor-evoked potential, *MKS* Marburg Competency Scale (Marburger Kompetenz Skala), *MMSE* Mini Mental State Examination, *MNA* Mini Nutritional Assessment, *PPT* Purdue Pegboard Test, *RTI* Reaction Time, *SF-36* Short Form-36 Health Survey, *SPPB* Short Physical Performance Battery, *SSP* Spatial Span, *T0* Baseline assessment, *T1* Assessment 1 after 60 days, *T2* Assessment 2 after 90 days, *TMS* Transcranial magnetic stimulation

